### Recruitment

Eligible participants will be identified at participating sites by clinicians involved in the management of eligible patient groups in both inpatient and ambulatory settings. Approved promotional material will target eligible patient groups to enhance recruitment.

### Randomisation

#### Sequence generation

Participants will be assigned to a study group based on their study-qualifying medical condition (table 1) using a central computer-generated randomisation sequence with a blocking factor of four created by the study statistician.

Participants in Group 1 will be stratified into one of two supra-stratum, haematological malignancy or systemic autoimmunity and then to sub-strata based on their planned treatment. Sub-strata include: haematological malignancy—chemotherapy; autoimmunity—B-cell depletion therapies; autoimmunity—anti-metabolite therapies; autoimmunity—TNFα-inhibition; autoimmunity—cyclophosphamide or alemtuzumab; autoimmunity—JAKi; autoimmunity—anti IL-17/23 monoclonal antibodies (table 1).

Group 1 participants will be randomised in a 1:1 ratio to receive either a COVID-19 booster at week 0 and a DT booster at week 24 (Arm A: immediate booster), or a DT booster at week 0 and a COVID-19 booster at week 24 (Arm B: deferred booster) (figure 1). Randomisation will be conducted using a central computer-generated random allocation algorithm using blocks and stratified by sub-strata population.

Group 2 has no sub-strata and participants will be randomised in a 1:1 ratio to receive either an immediate COVID-19 booster at week 0 (Arm C), or a deferred COVID-19 booster at week 24 (Arm D) (figure 1).

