### Trial design

CIRCUIT is an open-label, multicentre randomised clinical trial. Participants with a haematological malignancy or autoimmune/inflammatory disease will be randomised in a 1:1 ratio to receive either an additional COVID-19 booster pre-immunosuppression with a DT booster after 6 months of therapy or a DT booster pre-immunosuppression and an additional COVID-19 booster at 6 months. Participants at least 9 months post-BMT will be randomised in a 1:1 ratio to either receive a COVID-19 booster either following randomisation or after 6 months.

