### Allocation concealment mechanism

Following central computer randomisation, participants’ assignments to either immediate or deferred COVID-19 booster will appear on the screen. The randomisation screen will be printed and form part of participants’ study records. The screen print plus a prescription will be provided to an on-site clinical trials pharmacy for dispensing of the DT vaccine.

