### Blinding

This study was implemented in Sydney, Australia during the pandemic phase of COVID-19. During that time, the New South Wales (NSW) Ministry of Health had control over the limited supply of COVID-19 vaccine. Hence, we were unable to secure a supply of vaccines for the study. Therefore, the trial was designed so that COVID-19 boosters could be given within the state government mandated vaccination hubs and centres. As there were no supply or administration restrictions for the DT booster, it could be given to participants at the hospital study sites by research staff. Therefore, due to the different administration locations for the COVID-19 and DT vaccines, it was not possible to blind either the participants or research staff.

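### One fixed block size of four in an open-label trial leaves some allocations predictable: at most one in three to someone who sees a whole stratum list, far fewer to a single hospital

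*Protocol article*

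**What the plan says.** The section on sequence generation names one block size: "using a central computer-generated randomisation sequence with a blocking factor of four created by the study statistician". It returns to the method for Group 1: "Randomisation will be conducted using a central computer-generated random allocation algorithm using blocks and stratified by sub-strata population". Neither sentence mentions varying the size or withholding it from sites. Site is not named as a stratification factor.

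The ratio is equal in both groups: "Group 1 participants will be randomised in a 1:1 ratio" and "Group 2 has no sub-strata and participants will be randomised in a 1:1 ratio". Each block of four therefore holds two immediate and two deferred boosters.

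The Trial design section states that "CIRCUIT is an open-label, multicentre randomised clinical trial", and the Blinding section that "it was not possible to blind either the participants or research staff". Under Allocation concealment mechanism, participants' "assignments to either immediate or deferred COVID-19 booster will appear on the screen", and a print of the screen goes into the study record. That section describes only what happens after randomisation. Under Implementation, the site research team does the enrolling. Trial setting gives five hospitals, and Sample size gives 40 participants per sub-stratum, 280 in Group 1 and 40 in Group 2.

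**The concern.** Central randomisation protects the next assignment only if it cannot be worked out from earlier ones. With a single small block size and no blinding, the last one or two places of a block can sometimes be deduced by anyone who has seen the earlier places.

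There is a possible motive. The Objectives section accepts that deferring the booster may lead to more breakthrough infections, so a clinician might prefer a vulnerable patient to be in the immediate arm. There is some opportunity: treating clinicians identify candidates, and screening and randomisation may fall on the same day.

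At stake is the comparability of about 20 participants per arm in each sub-stratum. The planned within-stratum test is an unadjusted t-test. Adjustment is optional and depends on an imbalance being noticed.

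**Working it through.** The document gives no figure for predictability, so there is none to reproduce.

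**Inputs.** Block size 4, ratio 1:1, lists by sub-stratum (Sequence generation); 40 per sub-stratum, 280 and 320 in total (Sample size); five hospitals (Trial setting). I take the block size of four to apply to every list, including Group 2. Each hospital's share of a stratum is not given, so a range is shown.

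**Step 1: observer who sees the whole list and knows the block size.** Six arrangements of two A and two B are equally likely.
- Place 4 is always determined: 1 per block.
- Place 3 is determined when the first two match: 2/6 per block.
- Certain share = (1 + 1/3)/4 = 1/3, or 8 of the 24 places over the six arrangements.
- Best guess by place: 1/2, 2/3, 2/3, 1. Mean = 2.833/4 = 70.8%, against 50% with no information.

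As counts this is 40/3 = 13.3 per stratum, 280/3 = 93.3 in Group 1 and 320/3 = 106.7 overall. These are ceilings.

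**Step 2: one hospital that sees only its own patients.** Assume each enrolment in the stratum comes from this hospital with probability p, independently, and that it knows where its patients fall in the blocks.
- Place 3 is certain if both earlier places were its own and match: p²/3.
- Place 4 is certain if it saw both members of the arm already used up: p².
- Certain share of its own allocations = (p²/3 + p²)/4 = p²/3.

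Best-guess rates by place:
- place 1: 1/2
- place 2: 1/2 + p/6
- place 3: 1/2 + [1 − (1−p)²]/6
- place 4: p³ + (1−p)³/2 + [1 − p³ − (1−p)³] × 2/3

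The overall rate is the mean of the four. At p = 0.2 it is (0.500 + 0.533 + 0.560 + 0.584)/4 = 54.4%. The last column below is 40p × p²/3.

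| Share p | Certain, p²/3 | Best guess right | Certain allocations at that hospital, stratum of 40 |
|---|---|---|---|
| 20% | 1.3% | 54.4% | 0.1 |
| 40% | 5.3% | 58.1% | 0.9 |
| 60% | 12.0% | 61.7% | 2.9 |
| 80% | 21.3% | 65.7% | 6.8 |
| 100% | 33.3% | 70.8% | 13.3 |

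A simulation with equal recruitment agrees: 1.3% certain with five hospitals sharing a stratum, 3.8% with three, 8.3% with two. If the hospital does not know how many patients the others have enrolled, it can rarely or never exclude that the block has turned over, so fewer allocations are certain.

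**Step 3: effect of varying the block size.** Simulated lists of 40, with an observer who sees the whole list and knows which sizes are possible but not their order:

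| Blocks | Certain | Best guess right |
|---|---|---|
| 4 only | 33% | 71% |
| 4 and 6 | 5.6% | 68.9% |
| 4, 6 and 8 | 2.3% | 67.6% |

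Varying sizes removes most of the certainty but only a little of the guessing advantage.

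**The case against.** The strongest reply is that nothing gives a site sight of a stratum list. The lists are central, five hospitals recruit and site is not named as a stratification factor, so staff see only their own participants' assignments. No recruitment by site is reported, so concentration of a stratum at one hospital is conjecture. The article prints the block size, but does not say that sites knew it while enrolling. All of this stands. A reader might infer that one in three allocations is generally known in advance to site staff; the document does not support that.

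A reader might also infer that any steering would pass straight into the primary result. That goes too far. The endpoint is change from baseline, so a difference in starting titre is subtracted. Planned treatment, which bears on vaccine response, is the stratification factor. Linear regression adjustment is available if baseline characteristics are unbalanced. In Group 1 the window of at most two weeks before immunosuppression limits how long a patient could be held back. Nor does the text suggest that staff could choose which planned treatment is recorded. The protection is still partial: adjustment is optional, and unmeasured prognosis is covered by neither adjustment nor change from baseline.

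Finally, central permuted blocks of four are common, and separation of sequence generation from enrolment is already in place, since the study statistician creates the list and site teams enrol. That answers any criticism of who generates the list, but not of the single block size.

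**Conclusion.** The point holds as an avoidable weakness of limited size. One third certain, with 71% correct guesses, is an upper bound, reached only if one hospital fills nearly all of a stratum or hospitals share their assignments. For a hospital seeing only its own patients, certainty runs from about 1% to 21% as its share rises from 20% to 80%, even with block positions known. These figures assume that the observer knows the block size and that a hospital's enrolments are spread at random through the list. The document settles neither, and gives no recruitment by site. Nothing in it shows that selection bias occurred, or that any team could see a full list. The case for change rests on the low cost of a standard safeguard in a trial without blinding.

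**What to change.** For any allocations not yet made, have the study statistician regenerate the unused part of the central lists with randomly varying block sizes, for example 4 and 6, or 4, 6 and 8, within each sub-stratum and in Group 2. Keep the sizes out of documents that sites can read until recruitment closes.

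The work is small. The downside is balance: the largest mid-list difference between arms rises from 2 to 3 (with blocks of 6) or 4 (with blocks of 8). A stratum of 40, now exactly ten blocks ending 20 to 20, may end inside a block.

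If recruitment has closed, the lists cannot be changed. Report recruitment by site and stratum, which shows where in the table above each stratum falls, together with baseline balance by arm.

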**Trial registration number:**

NCT05415267.

STRENGTHS AND LIMITATIONS OF THIS STUDYFor the first time, a randomised clinical trial will be used to measure differences in seroconversion to a COVID-19 booster given at baseline versus at 24 weeks in adults commencing new or intensified moderate to severe immunosuppression.This study includes a variety of immunosuppressed adults including those with a haematological malignancy and a range of autoimmune/inflammatory diseases encompassing high burden diseases such as inflammatory bowel disease and multiple sclerosis as well as rarer conditions, sub-stratified by treatment type.The study has statistical power to analyse Group 1 participants as a whole or by distinct substrata-based type of immunosuppression.For pragmatic reasons not all types of conditions associated with immunosuppression are included in the study; exceptions include those with solid organ malignancy, renal transplant recipients, HIV-infected individuals and those with primary immunodeficiencies.In Australia, COVID-19 vaccines can only be administered in state-government mandated centres not by hospital study staff therefore blinding of participants and research staff as to which vaccine was given was not possible and is a limitation of the study.

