## Introduction

### Background and rationale

 It was recognised early in the COVID-19 pandemic that immunocompromised individuals were at increased risk of severe disease,^1 2^ delayed viral clearance^3 4^ and death^5 6^ compared with the general population. Immunocompromised individuals comprise heterogenous groups including, but not limited to, those with solid organ and haematological malignancies, those with autoimmune and inflammatory disease on immunosuppressive therapies, allogenic and autologous bone marrow transplantation (BMT) recipients and solid organ transplant recipients. While these groups were prioritised in many COVID-19 vaccine programmes, evidence soon followed that vaccine seroconversion, including titres of anti-SARS-CoV-2 spike protein IgG were lower in immunocompromised individuals compared with healthy comparators. Patients with follicular lymphoma treated with immunochemotherapy had lower anti-spike IgG following two doses of BNT162b2 vaccine compared with those who were untreated and to healthy controls.^7^ Similarly, in patients with Waldenström Macroglobulinemia, those receiving Bruton’s tyrosine kinase inhibitors (BTKis) had lower anti-spike IgG following two doses of BNT162b2 vaccine compared with untreated counterparts and healthy controls.^7^ Studies of a third dose of COVID-19 vaccine in patients with haematological malignancies have demonstrated heterogeneous improvement in anti-spike IgG levels dependent on disease state and therapy. A retrospective observational study of 381 patients with haematological malignancies who received a third dose of a mRNA COVID-19 vaccine found detectable anti-spike IgG in 73.1% of patients after two vaccine doses which rose to 86.4% after three doses.^8^ Rates of seroconversion were lower in patients with chronic lymphocytic leukaemia (CLL) (52.6%) and B cell lymphoma (60.9%).^8^ While the third vaccine dose improved seroconversion for patients on Janus kinase inhibitors (JAKi) (from 57.1% to 90.9%), the rates of seroconversion remained low for patients with haematological malignancies on anti-CD20 treatment (55%), the bcl-2 inhibitor venetoclax (50%) and BTKis (37.5%).^8^ An additional study of 172 patients with CLL/small lymphocytic lymphoma (SLL) who did not seroconvert after two doses of a BNT162b2 vaccine received a third dose of the same vaccine.^9^ Overall, 23.8% of patients with CLL/SLL seroconverted following the third BNT162b2 vaccine with the highest rates among patients who were treatment naïve (40.6%) or off treatment (40%) while lower seroconversion was observed among those on active treatment (12%).^9^ Only one of 28 patients who had received an anti-CD20 B-cell depletion agent in the preceding year seroconverted (3.6%).^9^

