#### Inclusion criteria

Adult aged ≥18 years with a medical condition included in table 1.Previously vaccinated with at least two doses of any licensed COVID-19 vaccine who requires initiation of moderate to severe immunosuppression; the most recent vaccination must have been given more than 3 months prior.Planned significant immunosuppressive therapy for at least 1 year (table 1).No cyclophosphamide, alemtuzumab or rituximab treatment in the past 5 years (concurrent corticosteroids with treatments listed in table 1 are permitted).Voluntary written informed consent.

**Table 1 T1:** Study populations

Group 1*	
**Haemato-oncology**	**Systemic autoimmunity**
Haematological malignancy (excluding bone marrow transplant recipients)† (n=40) B-CLL Follicular or marginal zone lymphoma Multiple myeloma Diffuse large B-cell lymphoma Other haemato-oncology condition at the discretion of the study PI or their delegate	ANCA-positive vasculitis,‡ ANCA-negative vasculitis,‡ Polyarteritis nodosa,‡ Churg-Strauss,‡ Ankylosing spondylitis,‡ Autoimmune hepatitis,§ IgG4 disease,‡ Inflammatory bowel disease,¶** Psoriatic arthritis,‡ Psoriasis, Rheumatoid arthritis,‡ SLE,‡ Sjogren’s syndrome,‡ Myasthenia gravis,†† Multiple sclerosis,‡‡ Autoimmune encephalitis, Neuromyelitis optica,¶ Bullous pemphigoid,¶ Pemphigus vulgaris¶ and variants, Sarcoidosis, Uveitis, other autoimmune/inflammatory conditions diagnosed by a specialist physician and at the discretion of the study PI or their delegate.
	B-cell depletion therapies, eg, rituximab, ocrelizumab, ofatumumab (n=40)
	Anti-metabolite therapies: azathioprine, calcineurin inhibitors, mycophenolate or methotrexate (moderate immunosuppression) (n=40)
	TNFα inhibition (with or without azathioprine or methotrexate or leflunomide to prevent anti-drug antibodies) (n=40)
	Cyclophosphamide or alemtuzumab (severe immunosuppression) (n=40)
	Janus kinase (JAK) inhibitors±leflunomide (n=40)
	Anti-IL-17 and/or 23 monoclonals, eg, secukinumab (n=40)

Group 2
*Bone marrow transplant (n=40)* Haematological malignancy—autologous or allogenic transplant (excluding for treatment of a primary immunodeficiency)

* Eligible patients with both a haematological malignancy and a systemic autoimmune condition are to be enrolled in the haematological malignancy sub-stratum.

† WHO criteria.

‡ EULAR criteria.

§ Biopsy proven.

¶ Mayo criteria.

** Crohn’s Disease activity index.

†† McDonnel I criteria.

‡‡ Must have AChR or Musk autoantibody positive.

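### The haematology sub-stratum is called chemotherapy but is filled by diagnosis, so its result averages over regimens and does not support the claims made by type of immunosuppression

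*Protocol article*

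**What the plan says.** Sequence generation divides Group 1 into haematological malignancy and systemic autoimmunity, and "then to sub-strata based on their planned treatment". Six autoimmunity sub-strata follow, each named by drug class. The only haematology entry reads "Sub-strata include: haematological malignancy—chemotherapy".

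Table 1 describes the same cell as "Haematological malignancy (excluding bone marrow transplant recipients)† (n=40", followed by B-CLL, follicular or marginal zone lymphoma, multiple myeloma, diffuse large B-cell lymphoma and "Other haemato-oncology condition at the discretion of the study PI or their delegate". No treatment is listed. A footnote adds: "Eligible patients with both a haematological malignancy and a systemic autoimmune condition are to be enrolled in the haematological malignancy sub-stratum". The eligibility rule on therapy, "Planned significant immunosuppressive therapy for at least 1 year (table 1", points back to that table.

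The strengths and limitations box describes the population as "sub-stratified by treatment type" and says the study has power for Group 1 as a whole or by type of immunosuppression. Outcomes lists chemotherapy and B-cell depleting therapies as separate modes for stratified immunological analyses. Statistical methods compares arms within each stratum by an unadjusted two-sample t-test. Regression adjustment may be used if baseline characteristics are unbalanced; no covariate is named.

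**The concern.** The two definitions do not agree. If chemotherapy is only a label, it misdescribes any haematology patient who starts a regimen without chemotherapy. If it is a restriction, haematology patients on other agents meet the eligibility criteria but have no sub-stratum. An analysis plan cannot settle this afterwards, because the stratum is assigned at randomisation.

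Elsewhere the article treats regimen as important. Autoimmune patients on B-cell depletion have their own cell; haematology patients on anti-CD20 agents do not. The background gives third-dose seroconversion in haematology patients by agent: "anti-CD20 treatment (55%), the bcl-2 inhibitor venetoclax (50%) and BTKis (37.5" per cent, against 86.4% in the whole cohort. At stake is what the result of this cell may be called, and whether variation between regimens erodes the power claimed for it.

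**Working it through.** **1. The definitions side by side**

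| Place | Basis of the haematology cell | Treatment named |
|---|---|---|
| Sequence generation | planned treatment | chemotherapy |
| Table 1, haemato-oncology column | diagnosis, with an open-ended entry | none |
| Table 1, dual-diagnosis footnote | diagnosis | none |
| Inclusion criterion on planned therapy | at least 1 year of significant immunosuppression, refers to Table 1 | none for haematology |

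Three of the four give no treatment basis. Assignment by diagnosis is the natural reading, and the label is the outlier.

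**2. The stated power**

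Inputs from Sample size: 40 per sub-stratum, so 20 per arm; difference 0.13 log10; SD 0.12 log10; two-sided 5%.

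- Standard error = 0.12 × √(2/20) = 0.0379.
- Non-centrality = 0.13 / 0.0379 = 3.43, with 38 degrees of freedom.
- Power = 91.6% by the noncentral t (92.9% by the normal approximation). The stated figure of over 90% reproduces.
- 10^0.13 = 1.35, which matches the stated 35%.

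This power belongs to the cell as a whole. For one regimen making up half of it (20 patients, 10 per arm), the same inputs give 63% (68% normal).

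**3. Illustration of the cost in precision**

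The article gives neither the regimen mix nor the effect of regimen on the endpoint. Assume that a share p of the cell is on anti-CD20 regimens and that these shift the time-weighted log10 titre change by d in both arms. Take 0.12 as the SD within a regimen; Sample size derives it from healthy vaccinees and infected patients. Then

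SD of the mixed cell = √(0.12² + p(1 − p)d²).

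| d (log10) | SD, p = 0.5 | Power, p = 0.5 | Power, p = 0.25 |
|---|---|---|---|
| 0 | 0.120 | 91.6% | 91.6% |
| 0.1 | 0.130 | 86.9% | 88.1% |
| 0.2 | 0.156 | 72.7% | 77.3% |
| 0.3 | 0.192 | 55.0% | 62.0% |

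**4. Is chance imbalance a further harm?**

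With p = 0.5, the hypergeometric probability that the arms differ by at least 20 percentage points in anti-CD20 use (4 of 20 patients) is 34%. At d = 0.3, a 20-point difference moves the estimate by 0.20 × 0.3 = 0.06, or 46% of 0.13. The variance of the unadjusted estimate already contains this:

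- within regimen: 0.12² × 2/20 = 0.00144;
- from regimen mix: 0.15² × 2/20 = 0.00225, where 0.15 = √(0.25) × 0.3;
- total 0.00369, standard error 0.0607, which equals 0.192 × √(2/20).

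So imbalance and the larger SD are one cost, not two. A simulation of this worst case under no timing effect rejects 5.1% of the time with the unadjusted t-test, so type I error is nominal.

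**5. Effect of adjustment**

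Under the same assumptions, including regimen (yes/no) as a covariate returns the residual SD to 0.12 with 37 degrees of freedom. Power is then about 91% (simulated 90.8% at d = 0.3).

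**The case against.** A reader might infer that the cell admits any treatment at all, that the background figures show the timing effect differing by regimen, and that imbalance in anti-CD20 use could create a false timing effect. The document supports none of these.

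- Participants must be starting moderate to severe immunosuppression planned for at least 1 year, with no cyclophosphamide, alemtuzumab or rituximab in the past 5 years. The background also speaks of immunochemotherapy for follicular lymphoma, so chemotherapy and anti-CD20 can belong to one regimen.
- The background figures are seroconversion levels, not differences between immediate and deferred boosting. They are mixed with disease: the same study gives 52.6% in CLL and 60.9% in B-cell lymphoma. The 90.9% on JAK inhibitors is not tied to any diagnosis named in Table 1.
- Randomisation keeps the comparison unbiased and type I error nominal, as step 4 shows.

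It is also fair that the 50% share and the shifts are assumptions and that the lowest power comes from the largest shift. Stratified analyses by mode of immunosuppression are already foreseen, and one pragmatic haematology cell is a legitimate choice. An anti-CD20 indicator would not separate BTK inhibitors or venetoclax, and splitting the randomisation of 40 patients in blocks of four could leave partial blocks.

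What remains is the contradiction between the two sections, the claim that does not fit this cell, and an adjustment that is optional, triggered by observed imbalance and without a named covariate.

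**Conclusion.** The point holds as an inconsistency of definition and a limit on interpretation. The haematology cell is assigned by disease while its label and the stated principle refer to treatment. Its result estimates an average timing effect over whatever haematology regimens are enrolled; it should not be reported as an effect under chemotherapy. One of the seven Group 1 sub-strata is affected, and the validity of the randomised comparison is not in question.

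The loss of precision is possible rather than shown. It ranges from about 5 points of power (91.6% to 86.9%) to about 37 points (to 55.0%) for shifts of 0.1 to 0.3 log10 with half the cell on anti-CD20 regimens, and is smaller at a quarter. These figures rest on an assumed mix, assumed shifts and a within-regimen SD of 0.12.

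**What to change.** 1. Make Sequence generation and Table 1 agree by naming the stratum by disease (haematological malignancy, excluding transplant recipients).
2. Limit the statements on sub-stratification and power by type of immunosuppression to the autoimmunity strata, and describe the haematology result as an average over regimens.
3. Prespecify planned anti-CD20-containing regimen (yes/no) as a covariate in the haematology analysis, in place of the unadjusted t-test there, and in the combined Group 1 analysis. Take it from the treatment plan as it stood before randomisation; Data collection methods already has that plan on the case report form.
4. Report haematology results by regimen descriptively, including BTK inhibitors and venetoclax, without a power claim.

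The cost is one degree of freedom and a few changes of wording. The randomisation lists need not change.

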
There are limited data to guide timing of booster vaccine administration around the commencement of moderate-to-severe immunosuppression. Current protocolised clinical guidelines for vaccination in the setting of immunodeficiency predominantly relate to two specific scenarios, those of splenectomy and BMT.

In planned or non-emergency splenectomy, vaccination is recommended at least 2 weeks prior to surgery to prevent overwhelming post-splenectomy infection particularly related to encapsulated bacteria.^16^ The pre-splenectomy schedule includes vaccination to Pneumococcus, meningococcal ACWY, meningococcal B, Haemophilus influenza type B (Hib) with booster doses to Pneumococcus, meningococcal ACWY and meningococcal B given at 2 months and 5 years in addition to a seasonal influenza vaccine.

Vaccination guidelines for adults who have undergone autologous or allogenic BMT advise a comprehensive re-vaccination programme commencing 6 months post-BMT.^16^ Revaccination is required for diphtheria/tetanus (DT; three doses total), Hib (three doses, 4 weeks apart), hepatitis B (three doses at 6, 8 and 12 months post-BMT), pneumococcus (three doses of a conjugate vaccine 4 weeks apart followed by two doses of a 23-valent vaccine), inactivated poliovirus (three doses, 4 weeks apart), MenACWY (two doses, 8 weeks apart), meningococcal B (two doses) and herpes zoster (two doses, 2–6 months apart) with an annual seasonal influenza vaccine also recommended. Additional vaccines given at 24 months post-BMT at the discretion of the treating physician include measles mumps and rubella (two doses, 4 weeks apart) and varicella zoster (two doses, 4 weeks apart) provided there is no evidence of graft-versus-host-disease, and immunosuppressive therapy has been ceased for more than 3 months.

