### Sample size

The maximum sample size is 320 participants, 280 in the systemic autoimmunity and haemato-oncology group and 40 in the BMT recipient group. This sample size is based on previously calculated integrated time-weighted AUC of live anti-SARS-CoV-2 NAb titres following two SARS-CoV-2 vaccinations in healthy adults^25^ and patients infected with COVID-19.^26 27^ SD calculated from these datasets were 0.11 log_10_ and 0.12 log_10_, respectively. Assuming an SD of 0.12 log_10_, the study will have over 90% power to detect a 0.13 log_10_ difference in time weighted AUC log_10_ change from baseline (2-alpha=5%) within each sub-stratum of 40 participants. This corresponds to a 35% difference in live virus neutralisation titre between randomised arms. Time-weighted AUC allows for varying of follow-up of participants due to missed visits, loss to follow-up or death. We conservatively estimate overall lost to follow-up to be 10% and mortality 1% balanced across randomised sub-strata.

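### Group 2 pools autologous and allogeneic transplants in a 20 versus 20 comparison whose main test ignores transplant type; type should be a pre-specified covariate

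*Protocol article*

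**What the plan says.** All references are to the protocol article.

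- **Population.** Table 1 defines Group 2 as "Haematological malignancy—autologous or allogenic transplant". The expected split between the two types is not given.
- **Size.** The sample size section plans "280 in the systemic autoimmunity and haemato-oncology group and 40 in the BMT recipient group". At 1:1 this is 20 per arm.
- **Allocation.** Under Sequence generation, "Group 2 has no sub-strata and participants will be randomised in a 1:1 ratio". The sequence is a "central computer-generated randomisation sequence with a blocking factor of four". Group 1, by contrast, is stratified by planned treatment.
- **Power.** "Assuming an SD of 0.12 log_10_, the study will have over 90% power" to detect 0.13 log10 at two-sided 5% in a sub-stratum of 40, the size that Group 2 also has. The SD comes from time-weighted titres "following two SARS-CoV-2 vaccinations in healthy adults^25^ and patients infected with COVID-19".
- **Analysis.** The statistical methods section compares arms within each stratum by a simple t-test without covariates. It allows linear regression adjustment if baseline characteristics turn out unbalanced, but as an option, with no covariate and no threshold named. Group 2 is presented separately, using similar methods where appropriate.

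**The concern.** Group 1 is stratified by type of immunosuppression, and the introduction describes large differences in vaccine response between treatments. In Group 2, transplant type is a plausible prognostic factor of the same kind. It is known at randomisation, yet it enters neither the allocation nor the main test. Blocks of four balance the arm sizes, not the mix of types.

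Group 2 stands alone, with no larger pooled estimate behind its 20 versus 20 comparison. If type predicts the change in titre, two things follow. A chance excess of one type in one arm moves the realised estimate. The between-type spread also stays in the residual variance of the unadjusted test, which costs power even when the arms happen to balance.

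The conditional clause does not settle the matter. It makes the choice of model depend on what the data show, in an open-label trial, and it does nothing for power when the arms are balanced.

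**Working it through.** **Inputs from the document:** 20 per arm; difference 0.13 log10; SD 0.12 log10; two-sided 5%; blocks of four; unadjusted t-test.

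**Assumed, because the document is silent:** D, the difference between the two types in time-weighted change from baseline (a constant difference in titre level would cancel); the share p of one type; and 0.12 as the SD within type.

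**1. The stated power.** Standard error = 0.12 × √(2/20) = 0.0379, and 0.13/0.0379 = 3.43. Power is 92.9% by the normal approximation and 91.6% by the noncentral t. Both agree with the plan's figure of over 90%.

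**2. Chance imbalance.** This is the hypergeometric distribution with 20 of the 40 going to each arm.

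| Split of types | Arms differ by 4 or more patients of one type (20 points) | By 6 or more (30 points) |
|---|---|---|
| 20 and 20 | 34% | 11% |
| 8 and 32 | 24% | 4% |

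**3. Shift in the unadjusted estimate.** A 20-point imbalance shifts it by 0.2 × D. At D = 0.12 this is 0.024, or 18% of 0.13. At D = 0.24 it is 0.048, or 37%.

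**4. Power of the unadjusted test.** Total SD = √(0.12² + p(1 − p)D²), put into the noncentral t. With p = 0.5:

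| D (log10) | Total SD | Power, unadjusted |
|---|---|---|
| 0 | 0.120 | 91.6% |
| 0.06 | 0.124 | about 90% |
| 0.12 | 0.134 | about 85% |
| 0.18 | 0.150 | 76% |
| 0.20 | 0.156 | 73% |
| 0.24 | 0.170 | 66% |

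With p = 0.2 the loss is smaller: 87% at D = 0.12 and 74% at D = 0.24.

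**5. Check by simulation.** 8,000 trials per setting, blocks of four, 20 of each type. Type I error is taken at no true difference and power at 0.13.

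| D | Stratified by type | Type I error, unadjusted | Power, unadjusted | Power, adjusted for type |
|---|---|---|---|---|
| 0 | no | 4.8% | 91.3% | 90.5% |
| 0.12 | no | 5.0% | 85.2% | 91.1% |
| 0.24 | no | 5.0% | 65.5% | 91.0% |
| 0.12 | yes | 3.0% | 86.5% | 91.5% |
| 0.24 | yes | 0.7% | 69.6% | 91.3% |

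The mean unadjusted estimate without stratification is 0.129 to 0.130 when the truth is 0.13, so there is no systematic bias. Adjustment recovers the power. Stratification with the t-test left unadjusted recovers little and makes the test conservative.

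**6. The other reading of 0.12.** If 0.12 is the total SD of the mixed population, the unadjusted power stays at 91.6%. The within-type SD is then √(0.12² − D²/4), for example 0.104 at D = 0.12, and adjustment would raise power above the stated level.

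**The case against.** In favour of the plan as it stands, the following can be said.

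- **Adjustment is provided for.** A reader might infer that the plan rules it out. It does not: regression is allowed when baseline characteristics are unbalanced, and similar methods extend to Group 2. This stands. What remains is that the provision is optional, triggered by the data and without a named covariate.
- **Chance imbalance is ordinary random error.** A reader might infer bias, or an imbalance that cannot be told apart from a timing effect. Neither is supported. Transplant type is known at randomisation, so an imbalance can be seen and adjusted for, and the simulation shows no systematic bias and a type I error near 5%.
- **The documents do not show that the types respond differently.** The background sets a condition on some vaccines after transplant, "provided there is no evidence of graft-versus-host-disease, and immunosuppressive therapy has been ceased for more than 3 months". It is tempting to read this as evidence of such a difference. But it concerns measles, mumps, rubella and varicella vaccines at 24 months and does not compare the types; the same paragraph gives both one re-vaccination programme. This stands, so transplant type is a plausible predictor and not a documented one.
- **The size of the loss is assumed.** This also stands. D = 0.20 exceeds the target effect of 0.13, and at D = 0.06 the loss is under 2 points.
- **Leaving 40 people unstratified is defensible, and covariates are commonly named in the analysis plan, which is not shown.** Both are fair. The point therefore does not rest on an omission. It concerns the unadjusted main test and the imbalance trigger, which the protocol does state.

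**Conclusion.** The point holds as a matter of efficiency and pre-specification. The protocol chooses an unadjusted main test for a small, separately presented comparison that mixes two transplant types, and leaves adjustment to a discretionary look at balance. A better method is available at almost no cost.

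The size depends on D. With 0.12 log10 as the within-type SD and a 50:50 split, the loss runs from under 2 points of power at D = 0.06 to about 7 at 0.12 and 26 at 0.24. It is smaller at an uneven split. If 0.12 is the total SD, nothing is lost against the stated power and a gain is forgone. The source of the SD favours the within-type reading, since neither dataset is described as containing transplant recipients, but the document does not settle it. On either reading the adjusted model is at least as good, apart from a loss of under 1 point if type has no effect.

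**What to change.** Before data lock, replace the unadjusted Group 2 t-test with a linear model of the primary outcome on randomised arm and transplant type (autologous versus allogeneic). Type enters as a fixed covariate whatever the observed balance. Report the arm difference by transplant type descriptively. The statistical methods section says that an analysis plan will be approved before data lock, so the change can be made there even if recruitment has ended.

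The cost is one degree of freedom (37 instead of 38 for error) and recording one baseline item. If type has no effect, power is about 91% instead of 91.6%.

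Stratifying any remaining Group 2 randomisation by type is optional and secondary. It needs one extra list and may leave an incomplete block in each stratum. It should not be done without the covariate.
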